#### 7.4.3 Context and rationale for follow up

For the primary outcome of death and secondary outcomes of progression free survival and toxic adverse side effects, we will implement an on-treatment follow up analysis with censoring as defined in table 6. For health-related quality of life outcomes, we will use panel measurements in accordance with the XYZ registry’s data collection schedule. Details of the analyses for health-related quality of life outcomes will be determined after further discussion.

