#### Table 2 Primary and secondary objectives and research questions

1. **Primary objective and research question**

| **Objective:** | To compare overall survival (OS) in patients > 18 years with metastatic [organ]carcinoma with a biomarker Y+ mutation who have shown progression after first line treatment and have indicated informed consent for longitudinal observational data collection as part of the XYZ Registry and are treated with a combination of Drug A and Drug B compared to controls who are treated with standard care for a period of a maximum of 2 years (or 4 years). Comparator patients will be included retrospectively as well prospectively. |
| --- | --- |
| **Hypothesis:** | Overall survival will be improved with Drug A and Drug B compared to standard of care. |
| **Population *(mention key inclusion-exclusion criteria):*** | Patients with biomarker Y+ positive metastatic [organ] cancer who progressed after at least of one line of treatment |
| **Exposure:** | Initiation of Drug A in combination with Drug B |
| **Comparator:** | Standard of care. In [anonymous country], SoC second line therapy is Drug C or in third line the SoC is Drug D. There will be 2 comparator arms. One will be initiation of Drug C or Drug D using concurrent years of data with the exposure arm. The other comparator group will be initiatiors of Drug C or Drug D using historical controls from years of data prior to availability of Drug A/B. |
| **Outcome:** | Overall Survival (OS) |
| **Time *(when follow up begins and ends):*** | Follow up from day after initiation of therapy until the first of outcome, discontinuation, add/switch therapy, disenrollment, end of study period, nursing home admission, death, progression of therapy, others to be discussed. |
| **Setting:** | Outpatient care |
| **Main measure of effect:** | Hazard Ratio (to be discussed). |

1. **Secondary objective 1 and research question**

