| **Population *(mention key inclusion-exclusion criteria):*** | Patients with biomarker Y+ positive metastatic [organ] cancer who progressed after at least of one line of treatment |
| **Exposure:** | Initiation of Drug A in combination with Drug B |
| **Comparator:** | Standard of care. In [anonymous country], SoC second line therapy is Drug C or in third line the SoC is Drug D. There will be 2 comparator arms. One will be initiation of Drug C or Drug D using concurrent years of data with the exposure arm. The other comparator group will be initiatiors of Drug C or Drug D using historical controls from years of data prior to availability of Drug A/B. |
| **Outcome:** | Resource utilization |
| **Time:** | Follow up from day after initiation of therapy until the first of outcome, discontinuation, add/switch therapy, disenrollment, end of study period, nursing home admission, death, progression of therapy, others to be discussed. |
| **Setting:** | Outpatient care |
| **Main measure of effect:** | Descriptive statistics (to be discussed) |

1. Research methods
   1. Study design

**Research design (e.g. cohort, case-control, etc.):** New user active comparator cohort study

**Rationale for study design choice:** In order compare the new treatment (Drug A/B) with standard of care (SoC), patients need to be followed from start treatment until censoring (death, progression, treatment failure, end of follow-up). Use of this design will help prevent time related biases such as depletion of susceptible, immortal time bias and adjustment for causal intermediates.

- 1. Study design diagram

[figure not shown]

- 1. Setting

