#### 7.4.2 Context and rationale for outcome(s) of interest

Overall survival is the primary outcome of interest. This is a hard outcome that is of great interest to patients, clinicians and policy decision makers. We will explore secondary outcomes such as progression free survival, health related quality of life, toxic adverse effects, and healthcare resource utilization.

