#### Table 8. Operational Definitions of Follow Up

|  |  |  |  |
| --- | --- | --- | --- |
| **Follow up start** | Day 1 |  |  |
| **Follow up end^1^** | **Select all that apply** |  | **Specify** |
| **Date of outcome** | Yes |  | See Table 5 |
| **Date of death** | Yes |  | Discharged dead or registry recorded death, whichever came 1st |
| **End of observation in data** | Yes |  | Allow 30 day gaps in enrolment |
| **Day X following index date**  *(specify day)* | Yes |  | Day 365 |
| **End of study period**  (specify date) | Yes |  | 30-Sep-15 |
| **End of exposure**  *(specify operational details,*  *e.g. stockpiling algorithm, grace period)* | Yes |  | **Stockpiling algorithm:** If refill occurs before end of days supply, count overlapping days at the end of the subsequent dispensing’s day supply.  **Grace period:** Bridge gaps of ≤30 days between dispensation + days supply and refill. Add 30 days to last dispensation + days supply in a treatment episode. |
| **Date of add to/switch from exposure**  *(specify algorithm)* | Yes |  | Date that patient in exposed group is dispensed comparator drug or vice versa |
| **Other date** *(specify)* | Yes |  | Nursing home admission |

^1^ Follow up ends at the first occurrence of any of the selected criteria that end follow up.

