#### Table 13. Power and sample size

1. Limitation of the methods

There are several potential limitations with the methods specified in this protocol.

1. Some important variables may not be collected or will be measured imperfectly
   1. We have selected validated algorithms when possible
   2. We have created proxies for important variables that are not directly captured in the data to reduce confounding by unmeasured factors
2. There will not be randomization
   1. We have emulated the design of a target trial
   2. We have balanced compared groups on important risk factors for the outcome(s)
3. On treatment follow up may be short in real-world practice, there is potential for informative censoring
   1. The results may not capture efficacy of long-term treatment but can measure effectiveness in populations as they are actually treated.
   2. We will do sensitivity analyses regarding reasons for censoring and incorporating censoring weights
4. Protection of human subjects

The study proposal has been reviewed and approved by the [redacted organization] ethics review board to ensure ethical treatment of human subjects as well as privacy protections. The proposed study is observational research that makes secondary use of data collected as part of routine care as well as patient reported outcomes. The project does not involve any intervention, alteration in standard clinical care or use of any procedure in patients. Therefore, there will be no adverse events related to the study itself. All personal identifiers will be encrypted. This encryption minimizes the risk of patient reidentification in the unlikely event of a breach in data security. The institution’s uses standard-issue virus protection software and access to data is controlled through the use of individual passwords known only to study staff. Study staff are required to complete the ABC training prior to being allowed to work on any data and are regularly re-certificated. As a further layer of privacy protection, cell sizes less than 11 will be suppressed in results tables.

1. Reporting of adverse events

The proposed study is observational research that makes secondary use of data collected as part of routine care and does not involve any intervention or alteration in clinical care. Therefore, reporting of adverse events related to this study is not applicable. Safety evaluations for this study are limited to the specified safety outcomes stated in section 4.4.2.

1. References

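### The primary overall-survival analysis stops follow-up when treatment ends, so its hazard ratio describes death on treatment rather than overall survival, and the power figure makes no allowance for the deaths this leaves out

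*Protocol*

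**What the plan says.** Section 7.4.2 states "Overall survival is the primary outcome of interest", and the primary objective in Table 2 is a comparison of overall survival. For death, section 7.4.3 then says "we will implement an on-treatment follow up analysis with censoring as defined in table 6". Table 6 defines exposure groups and holds no censoring rules; these are in Table 8.

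Three places list what ends follow-up, and they differ:

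- **Table 2, primary objective, Time row:** "until the first of outcome, discontinuation, add/switch therapy, disenrollment, end of study period, nursing home admission, death, progression of therapy", with further stops still open.
- **Section 7.1:** patients are followed "until censoring (death, progression, treatment failure, end of follow-up".
- **Table 8 (operational):** end of exposure, with the rule "Add 30 days to last dispensation + days supply in a treatment episode"; add/switch, defined as "Date that patient in exposed group is dispensed comparator drug or vice versa"; "Nursing home admission"; also Day 365, death and end of observation. The earliest applies. Progression is not listed.

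The primary model in Table 10 is a Cox model with exposure as the only term and no censoring weights. Section 8 concedes that "On treatment follow up may be short in real-world practice, there is potential for informative censoring" and promises sensitivity analyses by reason for censoring and with censoring weights. Table 11, where these would be specified, is still open.

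Section 7.9 expects about 5,000 exposed patients, 35% deaths over one year, 1:1 matching and more than 80% power for an HR of 0.90.

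**The concern.** In metastatic cancer, patients who stop or change treatment, progress or enter a nursing home tend to be those whose outlook has worsened. A Cox model needs censoring to be unrelated to the later risk of death, given what is in the model. Here the model contains only exposure, and the censoring events are linked to prognosis, possibly to a different degree in each arm.

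The estimate then answers another question: how often patients die while on their first study drug or within 30 days of its end. A survival gain that comes from delaying progression, or a harm that appears after treatment, falls largely outside that window. The objective and hypothesis concern overall survival, and the protocol expects the results to inform coverage and reimbursement, so the mismatch affects what the main result means. Fewer counted deaths also undermine the power statement.

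**Working it through.** **1. The plan's power figure.** Inputs from section 7.9: 5,000 exposed, 1:1 matching, 35% one-year deaths, HR 0.90. Assumed: two-sided 5%, in line with the 95% confidence interval in Table 10. Schoenfeld: power = Φ(√D/2 × |ln HR| − 1.96), with |ln 0.90| = 0.1054.

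- 35% in both arms: D = 10,000 × 0.35 = 3,500; √3,500/2 × 0.1054 = 3.117; Φ(3.117 − 1.96) = 87.6%.
- 35% in controls, HR 0.90 in the exposed: exposed risk = 1 − 0.65^0.9 = 32.1%; D = 5,000 × (0.35 + 0.321) ≈ 3,357; power 86.3%.

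The stated figure is reproduced, provided all one-year deaths count. (Taking 5,000 as the total gives 1,750 deaths and 59.6%, so 5,000 per arm is the reading that fits.)

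Deaths needed for 80%: 4 × (1.960 + 0.842)² / 0.1054² ≈ 2,829. The margin is 1 − 2,829/3,500 = 19% or 1 − 2,829/3,357 = 16%. If half of 3,500 deaths are lost, power is 59.6%; if 70% are lost, 40.0%.

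**2. How many deaths the Table 8 discontinuation rule keeps.** Treatment duration is not in the protocol, so a range of medians m (months) is assumed. Stopping is exponential with μ = ln 2/(30.4m) per day; death has λ = −ln(0.65)/365 = 0.00118 per day. If stopping is unrelated to risk, the proportion of patients with a counted death is

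1 − e^(−30λ) + e^(−30λ) × λ/(λ+μ) × (1 − e^(−335(λ+μ))),

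and dividing by 0.35 gives the share of deaths kept. The third column (simulated) lets the death hazard triple after stopping, with one-year mortality still 35%.

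| Assumed median treatment | Share kept, stopping unrelated to risk | Share kept, hazard triples | Power, stopping unrelated to risk |
|---|---|---|---|
| 2 months | 35% | 23% | 46% |
| 3 months | 45% | 29% | 55% |
| 4 months | 53% | 34% | 62% |
| 6 months | 63% | 44% | 70% |
| 9 months | 72% | 54% | 76% |
| 12 months | 78% | 61% | 79% |

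Every share is below the 81% (2,829/3,500) needed for 80% power. Switch and nursing home stops would lower them further.

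**3. What happens to the hazard ratio.** Simulated illness-death model over one year, all hazards assumed. Benefit case: death 0.10 per year before and 0.80 after progression; progression 2.0 per year on standard care and 1.5 on Drug A/B. Harm case: progression 2.0 in both arms; death after progression 1.2 on Drug A/B against 0.80.

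| Follow-up | Benefit HR | Counted as deaths, standard care / A/B | Harm HR |
|---|---|---|---|
| To death or one year | 0.87 | 37% / 33% | 1.39 |
| Censored at progression | 1.00 | 4.2% / 5.0% | 1.00 |
| Censored at progression + 30 days | 0.88 | 9.4% / 9.7% | 1.27 |

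The middle row is 1.00 by construction, because the pre-progression death hazard is 0.10 in both arms; simulated values lie between 0.99 and 1.00. Simulated values for the 30-day benefit case lie between 0.88 and 0.89.

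A second set uses time to stopping plus 30 days, with death at 0.0005 per day on treatment and three times that afterwards. With median treatment of 3 against 6 months, the ratio of death rates is 0.82 over all follow-up and 0.88 on treatment. With 3 months in both arms and a post-treatment hazard of 4 against 3 times, it is 1.25 and 1.13.

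**The case against.** On-treatment follow-up is a recognised estimand. The document is a declared draft, and section 8 names informative censoring and commits to weighted sensitivity analyses. That is fair, but the on-treatment choice for death is not marked as open, and a sensitivity analysis does not bring the primary estimate into line with an overall-survival objective.

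Four stronger readings are tempting, and the documents do not support them:

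- **Most deaths are lost.** No figure in the protocol shows this. In the table above it holds up to about 3 months' median treatment if stopping is unrelated to risk, and up to about 6 months if the hazard triples.
- **A real benefit disappears.** The HR of 1.00 needs censoring at progression with no grace period, which Table 8 does not list. With 30 days' grace the same example gives 0.88 against 0.87, so the loss there is mainly of events. The harm is attenuated, not hidden.
- **Nothing in the data calls for censoring.** Death records are linked, but Table 7 gives 93% sensitivity for death and nothing on completeness by care setting.
- **Later resource use is never counted.** Table 2 does give resource use the same stops, but its measure and model are still to be discussed, and section 7.4.3 does not put resource use under the on-treatment rule.

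**Conclusion.** The point stands and should be settled before the protocol is registered. As written, the primary analysis estimates death during treatment plus 30 days, by an unweighted model with prognosis-related censoring, and reports it as overall survival. This follows from the text alone and does not depend on any simulation.

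The size is less certain. The share of deaths lost and the bias depend on treatment duration and on hazards that the protocol does not state, so the hazard ratios above are illustrations. The bias was small in one example with the grace period and material in the others. The power consequence is firmer: it uses the protocol's own 5,000, 35% and 0.90, with a two-sided 5% level assumed, and shows that losing 16-19% of deaths is enough to fall below 80%.

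The disagreement of Table 2 and section 7.1 with Table 8 over progression is a separate, plain contradiction. Discontinuation, switch and nursing home admission would still censor informatively if progression were removed everywhere.

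**What to change.** - **Primary analysis.** In section 7.4.3, Table 2 and Table 8, follow every patient for overall survival from Day 1 to death or administrative end of data, without censoring at discontinuation, add/switch, progression or nursing home admission.
- **Sensitivity analysis.** Enter the on-treatment analysis in Table 11 by name, with the censoring weights that section 8 promises.
- **Consistency.** Reconcile the end-of-follow-up lists in Table 2, section 7.1 and Table 8, and point section 7.4.3 to Table 8. State one administrative end: Table 8 has Day 365, while the objective has 2 (or 4) years.
- **Power.** State in section 7.9 that the 35% counts all one-year deaths. Under the revised primary analysis at one year, the figure stands at 86-88%.

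The cost is mainly wording. Follow-up past treatment should need no new data, since deaths are linked by a universal identifier, but completeness of death capture after treatment ends and in nursing homes should be confirmed. The drawback is that later crossover dilutes the contrast; the weighted on-treatment analysis addresses that.

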#### Table 8. Operational Definitions of Follow Up

|  |  |  |  |
| --- | --- | --- | --- |
| **Follow up start** | Day 1 |  |  |
| **Follow up end^1^** | **Select all that apply** |  | **Specify** |
| **Date of outcome** | Yes |  | See Table 5 |
| **Date of death** | Yes |  | Discharged dead or registry recorded death, whichever came 1st |
| **End of observation in data** | Yes |  | Allow 30 day gaps in enrolment |
| **Day X following index date**  *(specify day)* | Yes |  | Day 365 |
| **End of study period**  (specify date) | Yes |  | 30-Sep-15 |
| **End of exposure**  *(specify operational details,*  *e.g. stockpiling algorithm, grace period)* | Yes |  | **Stockpiling algorithm:** If refill occurs before end of days supply, count overlapping days at the end of the subsequent dispensing’s day supply.  **Grace period:** Bridge gaps of ≤30 days between dispensation + days supply and refill. Add 30 days to last dispensation + days supply in a treatment episode. |
| **Date of add to/switch from exposure**  *(specify algorithm)* | Yes |  | Date that patient in exposed group is dispensed comparator drug or vice versa |
| **Other date** *(specify)* | Yes |  | Nursing home admission |

^1^ Follow up ends at the first occurrence of any of the selected criteria that end follow up.

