#### Table 3 Operational Definition of Time 0 (index date) and other primary time anchors

| **Study population name(s)** | **Time Anchor Description**  **(e.g. time 0)** | **Number of entries** | **Type of entry** | **Washout window** | **Care Setting^1^** | **Code Type^2^** | **Diagnosis position** | **Incident with respect to…** | **Measurement characteristics/**  **validation** | **Source of algorithm** |
| --- | --- | --- | --- | --- | --- | --- | --- | --- | --- | --- |
| **Exposure**  Drug A/B | Date of incident dispensation of Drug A/B (time 0) | Single | Incident | [-∞, 0] | n/a | ATCC | n/a | Drug A or Drug B alone, Drug A/B in combination, Drug D | No validation study | Investigator review of drug codes  XYZ registry dispensing data years 2021-2022 |
| **Comparator 1**  (concurrent)  Standard of Care (SoC).  Drug C or Drug D | Date of incident dispensation of standard care  (time 0) | Single | Incident | [-∞, 0] | n/a | ATCC | n/a | Drug C initiators must be incident with respect to Drug A, B, C and D  Drug D initiators must be incident with respect to Drug A, B, D but not C. | No validation study | Investigator review of drug codes  XYZ registry dispensing data years 2021-2022 |
| **Comparator 2**  (historical)  Standard of Care (SoC).  Drug C or Drug D | Date of incident dispensation of standard care (time 0) | Single | Incident | [-∞, 0] | n/a | ATCC | n/a | Drug C initiators must be incident with respect to Drug A, B, C and D  Drug D initiators must be incident with respect to Drug A, B, D but not C. | No validation study | Investigator review of drug codes  XYZ registry dispensing data years 2019-2020 |

^1^ IP = inpatient, OP = outpatient, ED = emergency department, OT = other, n/a = not applicable

^2^See appendix for listing of clinical codes for each study parameter

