#### Table 12. Metadata about data sources and software

|  | **Data 1** | **Data 2** |
| --- | --- | --- |
| **Data Source(s):** | XYZ Data Registry (concurrent/prospective) | XYZ Data Registry (historical) |
| **Study Period:** | Jan 1, 2021- Dec 31, 2022 | Jan 1, 2019- Dec 31, 2020 |
| **Eligible Cohort Entry Period:** | Jan 1, 2021- Dec 31, 2022 | Jan 1, 2019- Dec 31, 2020 |
| **Data Version (or date of last update):** | V2.0 – V5.0 | V1.0 |
| **Data sampling/extraction criteria:** | All patients > 18 years with metastatic [organ] carcinoma with a biomarker Y+ mutation who have shown progression after first line treatment and are treated with a combination of Drug A/B or with standard care | All patients > 18 years with metastatic [organ] carcinoma with a biomarker Y+ mutation who have shown progression after first line treatment and are treated with standard care |
| **Type(s) of data:** | Patient registry data including linked electronic health records, insurance claims, death, and patient reported outcomes | Patient registry data including linked electronic health records, insurance claims, death, and patient reported outcomes |
| **Data linkage:** | Linked based on universal patient identifier in [anonymous country] | Linked based on universal patient identifier in [anonymous country] |
| **Conversion to CDM*:** | n/a | n/a |
| **Software for data management:** | SAS 9.4, My SQL 15.0.2000.5 | SAS 9.4, My SQL 15.0.2000.5 |

*CDM = Common Data Model

- 1. Data management

The research team operates a secure, state-of-the-art, computing facility. The computer cluster is Linux-based and offers SAS 9.4, Stata 15.1, and R. The data center is a secure facility that houses both our computing environment as well as clinical systems and electronic medical records for several large hospitals in WA. Entry into the computer room requires passing through staffed building security, a successful palm scan, and then passing through staffed computer room security. The research machines are connected to the networking backbone with 10 gigabit-per-second fiber links. Network security is overseen by Information Security, who apply the same standards used for the hospitals electronic medical records systems to the research teams data. All data are transmitted to programmers' workstations in an encrypted state. Backups are created using 256-bit AES encryption, the current Department of Defense standard for data security, and are stored in a locked facility.

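### Table 8 sets the end of the study period at 30 September 2015, more than three years before any patient can enter, so the OS, PFS and toxicity hazard ratios cannot be estimated as specified

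*Protocol*

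**What the plan says.** Table 8 (section 7.4.3) defines when follow-up starts and stops. It starts the day after the index date ("Follow up start | Day 1"). Among the selected end criteria are Day 365 and the end of the study period, whose row reads "specify date) | Yes | | 30-Sep-15". The footnote combines the criteria: "Follow up ends at the first occurrence of any of the selected criteria that end follow up".

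Table 12 gives different calendar dates for the concurrent and historical data: "Study Period: | Jan 1, 2021- Dec 31, 2022 | Jan 1, 2019- Dec 31, 2020". The entry window is the same: "Eligible Cohort Entry Period: | Jan 1, 2021- Dec 31, 2022 | Jan 1, 2019- Dec 31, 2020". Table 3 agrees. Index dispensings for Drug A/B and the concurrent comparator come from "XYZ registry dispensing data years 2021-2022", and those for the historical comparator from "XYZ registry dispensing data years 2019-2020".

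Table 2 lists the end of the study period as a follow-up end for the primary objective and each secondary objective. Section 7.4.3 applies on-treatment censoring to death, PFS and toxicity and refers to Table 6 for the definition. Table 6 only says that assessment runs from day 1 to censoring; the criteria themselves are in Table 8.

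**The concern.** An administrative end date that precedes every possible index date leaves no observation time. Table 8 is the only place where the follow-up ends named in Table 2 are made operational, so this is a censoring rule and not background text. The title-page disclaimer says that open decisions are marked as to be discussed or determined. This cell is not marked that way; it holds a firm date.

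What is at stake is the primary hazard ratio and those for PFS and toxicity. The choice of replacement date also matters, because it decides how much of the one-year follow-up assumed in section 7.9 second-year entrants can have.

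**Working it through.** **1. The dates as written.** Inputs: stop date 30 Sep 2015 (Table 8); entry windows from Table 12, consistent with Table 3. Gap = entry date − stop date; years = days / 365.25.

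| Entry date | Days after stop date | Years |
| --- | --- | --- |
| Earliest historical, 1 Jan 2019 | 1,189 | 3.26 |
| Last historical, 31 Dec 2020 | 1,919 | 5.25 |
| Earliest Drug A/B or concurrent, 1 Jan 2021 | 1,920 | 5.26 |
| Last Drug A/B or concurrent, 31 Dec 2022 | 2,649 | 7.25 |

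Follow-up time = earliest end criterion − start. The 2015 date is before the start for every patient, so follow-up is negative in all three groups and no event is counted.

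**2. An alternative reading of the cell.** If it meant 15 September 2030, it would still contradict Table 12, and it would fall after the final report of 2023-09-01 (Table 1).

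**3. The stated power.** Section 7.9 gives about 5,000 exposed patients, 1:1 matching, 35% deaths over one year and HR 0.90. It states no alpha; I assume 0.05 two-sided, from the 95% interval in Table 10. By Schoenfeld, power = Φ(½·√D·|ln HR| − 1.96).

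- Taking 35% as the pooled rate: D = 10,000 × 0.35 = 3,500. ½ × 59.16 × 0.1054 = 3.117, and Φ(3.117 − 1.96) = 87.6%.
- Taking 35% as the comparator rate: hazard h = −ln 0.65 = 0.431. The exposed rate is 1 − exp(−0.9h) = 32.1%, so D = 5,000 × (0.350 + 0.321) = 3,357 and power is 86.3%.

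The stated figure is reproduced if 5,000 is the exposed arm. About 2,829 deaths are needed for 80% power.

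**4. The same calculation with the Table 12 end dates.** Entry and study period close on the same day in each cohort. In the concurrent cohort, an entrant on 31 Dec 2021 reaches Day 365 on 31 Dec 2022, and anyone entering later does not. In the historical cohort, which includes a leap year, the last entrant to reach Day 365 enters on 1 Jan 2020.

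Assume uniform entry over the two years and a constant hazard. First-year entrants have a full year. Second-year entrants have between zero and one year. The probability of an observed death is

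p(h) = ½·(1 − e^(−h)) + ½·[1 − (1 − e^(−h))/h].

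- 35% pooled: p = ½ × 0.350 + ½ × (1 − 0.350/0.431) = 0.269. D = 2,688, power 78.0%.
- 35% in the comparator: p = 0.269 (comparator) and 0.246 (exposed). D = 5,000 × (0.269 + 0.246), or 2,575 before rounding; power 76.2%.

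Both event counts fall short of 2,829. On-treatment censoring is not included and would lower them further.

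**5. The data lock.** Table 1 puts protocol registration and data lock or freeze at 2022-03-01. That is ten months before the concurrent study period ends in Table 12. Table 12 lists data versions 2.0 to 5.0 for this cohort, so successive extracts may be intended, but the protocol does not say which one the lock concerns.

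**The case against.** The contradiction itself has no good rebuttal: the cell is intact, its date is firm, and nothing elsewhere overrides it. The fair objections concern scope and harm.

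- **It would be noticed.** A stop date before all entry fails at once when programmed, so it would not silently bias a hazard ratio. Table 12 already records a study period for each cohort, and this is a V1 draft with later versions expected. This stands. It limits the harm but does not make the rule usable.
- **Not clearly every endpoint.** A reader might infer that all outcomes are lost. Section 7.4.3 handles quality of life by panel measurements with analysis details open, and section 7.5.1 defers the resource-use models. Table 2 does list the same end for those objectives, but the effect is secure only for OS, PFS and toxicity.
- **No evidence of a cut-off chosen on results.** A reader might also infer that the replacement date would be picked once outcomes are visible. The protocol does not say or imply this, and Table 12 offers an obvious candidate.
- **Different dates by cohort are not a fault.** The historical and concurrent cohorts cover different years, so their end dates should differ. What is needed is that each is stated.

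**Conclusion.** The point holds as an internal contradiction in an operative censoring rule and must be corrected before programming. The date conflict rests on no assumption: the stop date is 1,189 days before the earliest historical entry and 1,920 days before the earliest Drug A/B or concurrent entry. That no patient contributes follow-up is the literal result of the rule, not a forecast of what analysts would do.

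Copying the Table 12 dates into Table 8 would restore estimability but leave a smaller problem. Power for the concurrent contrast would be about 76% to 78%, against the stated figure above 80%. That range depends on uniform entry, constant hazard, two-sided 0.05 and 5,000 matched pairs, and it ignores on-treatment censoring.

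**What to change.** 1. In Table 8, replace the 2015 date with an explicit administrative end date for each cohort: one for Drug A/B and comparator 1, one for comparator 2. Make Table 12 carry the same dates.
2. Choose one of two routes and state it. Either keep 31 Dec 2022 and 31 Dec 2020, say that second-year entrants have truncated follow-up, and restate the section 7.9 power for the concurrent contrast on that basis. Or set a follow-up end later than the end of entry in both tables. A full 365 days for the last concurrent entrant would run to 31 Dec 2023, after the 2023-09-01 final report, so that milestone would need to be checked as well.
3. Reconcile the chosen dates with the 2022-03-01 data lock in Table 1, saying which extract the lock concerns.
4. In section 7.4.3, change the Table 6 reference to Table 8.

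The cost is a few text edits across Tables 1, 8 and 12 and section 7.4.3, plus one rerun of the power calculation under the first route. The second route may also need a later data extract and a later report.
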